## Alteration of small bowel water in IBS

Small bowel water content has been previously difficult to assess. Seven to eleven litres of fluid passes through the upper digestive system per day. However the majority (80%) is absorbed so that only 2 litres enters the colon[47]. There is a natural balance between the excretion and absorption of fluid within the gastrointestinal system, which if disturbed can lead to diarrhoea or constipation.

Until recently studies required intestinal intubation and perfusion or aspiration of low viscosity liquid ‘meals’ which do not mimic normal physiological states and can influence gastrointestinal function. New MRI techniques have now been developed[48] and have shown a reduction in small bowel water content (SBWC) of fasted D-IBD patients compared to healthy volunteers[49]. This reduction can be mimicked by intravenous injections of corticotrophin releasing factor (CRF), a mediator of the stress response which IBS patients are know to be hypersensitive to. Stress in known to be important in the pain and diarrhoea in IBS and similar effects could be present in diverticular disease where diarrhoea predominates. Stress also activates mucosal mast cells and may contribute to the proinflammatory bias of the mucosal immunocyutes seen in IBS. Whether adipokines can exacerbate this remains to be demonstrated.

# STUDY OBJECTIVES AND PURPOSE

## Aim

1. To determine differences in adipose deposition and adipokines on diverticular disease symptoms and small bowel water using MRI in participants.

## PURPOSE

## Hypotheses

1. DD Patients with a higher proportion of visceral fat will have increased incidence of painful symptoms and loose stool compared to patients with higher subcutaneous fat distribution.
2. Patients with DD symptoms will have decreased levels of adipokines compared non-symptomatic DD controls but have increased levels of circulating pro-inflammatory cytokines.
3. Patients with diarrhoea predominant diverticular disease will show similar MRI results to D-IBS patients, having reduced fasting small bowel water content and a narrower gastrointestinal lumen diameter (contracted small bowel) but increased colonic water.

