## Altered bowel habit and diverticular disease

Persistent or intermittent alteration of bowel habit is a common complaint in patients with diverticulosis and diverticular disease. A recent study suggests that 28.5% of patients with diverticulosis have altered bowel habit[39] and 16.5% frequent lower abdominal pain. Diverticular patients often complain of constipation (11.7% functional and 18.4% chronic) and/or diarrhoea (6.4% functional and 12.2% chronic)[39]. This is especially the case in the over 65yrs age group there is a correlation between diarrhoea predominant IBS (OR 1.9 95% CI 1.1 - 3.3 P 0.02) and mixed IBS (OR 3.0 95%CI 1.2 - 7.4 P 0.02) and diverticulosis[39].

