## SECONDARY OBJECTIVES

Differences between:

1. Adiponectin and leptin serum levels between symptomatic and asymptomatic DD groups
2. The incidence of diarrhoea between participants with a BMI <25Kgm-2 and those >25Kgm-2.
3. Adiponectin and leptin serum levels between DD groups with and without diarrhoea
4. Small and large bowel water and lumen diameter in symptomatic and asymptomatic DD groups
5. Calprotectin levels between symptomatic and asymptomatic DD groups.
6. Microbiological gut profile between symptomatic and asymptomatic DD groups.

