# Methods

## Participant groups

We will recruit n = 35 participants in each group (Total 105). Participants will include;

- 1. 35 participants with symptomatic DD and a patient heath questionnaire 15 score of >7
  2. 35 participants with symptomatic DD and a patient heath questionnaire 15 score of <7
  3. 35 participants with asymptomatic DD

The DD groups will be age and sex matched.

Having excluded those with e.g severe co-morbidity, alcoholism or drug dependence or inability to give informed consent (see exclusion criteria), we will invite participation in the MRI study day.

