## MRI study day protocol

Participants will be required to make 1 visit to the department. Prior to the visit we will ask participants to complete a 14 day bowel habit diary sheet and provide a stool sample, to bring on the day of their MRI visit.

The participants will visit the ***Brain and Body Centre*** after a overnight fast (fast of 12 hrs food and 6 hr for clear fluids). They will be asked to omit any laxatives for 24hrs and antispasmodics for 12hrs prior to the MRI study day. The participants will be screened and consented for the MRI study. They will have baseline pulse, blood pressure, height and weight, waist and hip circumference measured and recorded and will complete a safety questionnaire to ensure there are no contraindications to MRI (i.e. have metal implants or pacemaker).

Participants will be shown the 1.5T MRI Philips Achieva scanner. They will be positioned supine in the scanner with a parallel imaging body coil wrapped around the abdomen. Several different imaging sequences will used to optimally image the different regions of the gut as follows;

1. SBWC will be assessed with a single shot, fast spin echo sequence. This scan will take approximately 10 minutes.
2. A dual-gradient echo imaging sequence will be used to visualize anatomy. This scan will take approximately 10 minutes.

Including set-up and imaging, the volunteers spend approximately 20 minutes inside the magnet.

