### Inclusion criteria

1. Participants must have symptomatic and asymptomatic Diverticular disease confirmed on endoscopy/ *telescope test, barium enema or CT scan*

*(Symptomatic disease is define as lower abdominal pain >1hr on 3 or more days per month for longer than 3 months.)*

1. 18 – 85 years of age.
2. Signed informed consent

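### Hypothesis 3 concerns diarrhoea-predominant DD, but the only MRI bowel-water and lumen endpoint compares groups defined by pain, so no listed endpoint tests it

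*Protocol*

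**What the plan says.** Hypothesis 3 (Protocol, Hypotheses) reads: "Patients with diarrhoea predominant diverticular disease will show similar MRI results to D-IBS patients, having reduced fasting small bowel water content". It goes on to predict a narrower gastrointestinal lumen and increased colonic water. The population is defined by bowel habit.

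The matching endpoint is number 4 under Secondary Objectives, repeated in the synopsis: "Small and large bowel water and lumen diameter in symptomatic and asymptomatic DD groups". Its groups are defined under Inclusion criteria: "Symptomatic disease is define as lower abdominal pain >1hr on 3 or more days per month for longer than 3 months". Bowel habit plays no part in that definition. Nor does it in the three recruited groups (Participant groups), which are formed from the pain definition and the PHQ-15 score, for example "35 participants with symptomatic DD and a patient heath questionnaire 15 score of >7". No D-IBS or healthy-volunteer group is recruited.

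A split by diarrhoea does appear in the plan, but for serum markers only. Secondary endpoint 3 is "Adiponectin and leptin serum levels between DD groups with and without diarrhoea". Secondary endpoint 2 compares the incidence of diarrhoea by BMI. Bowel habit is recorded: before the visit participants are asked to "complete a 14 day bowel habit diary sheet and provide a stool sample" (MRI study day protocol).

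**The concern.** The hypothesis and its endpoint divide the participants along different lines. Someone with pain and constipation counts as symptomatic. Someone with diarrhoea but without the qualifying pain falls outside the symptomatic definition and could sit in the comparison group, which would pull the contrast against the hypothesis. If reduced small bowel water belongs to diarrhoea, the pain contrast sees only as much of it as the two groups differ in their share of diarrhoea.

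The result would then be hard to interpret either way. A null finding on endpoint 4 would say little about hypothesis 3, and a positive one could reflect pain rather than diarrhoea. If the right contrast is added only after the data are seen, it becomes post hoc. Small bowel water is named in the study's single stated aim, and this is one of three hypotheses.

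**Working it through.** **Plan's own figure.** The protocol has no power statement for bowel water. Its one sample-size figure, 35 per group, is for a 30% difference in visceral fat at 90% power, with no SD given. Back-solving two-sided gives SD = 0.30 / [(1.960 + 1.282) × √(2/35)] = 38.7% of the mean, or d = 0.30/0.387 = 0.775. That concerns visceral fat and does not bear on this point.

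**Inputs from the protocol.** Two symptomatic groups of 35 and one asymptomatic group of 35, so endpoint 4 taken as written is 70 vs 35. Tests are two-tailed; the 5% level is taken from the sample-size statement. The background section on altered bowel habit gives "Diverticular patients often complain of constipation (11.7% functional and 18.4% chronic) and/or diarrhoea (6.4% functional and 12.2% chronic"). Those rates describe diverticular patients in general, not patients selected for pain.

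**Assumptions.** The protocol gives neither a bowel-water effect size nor the diarrhoea shares in its groups. I assume a shift of δ SD confined to participants with diarrhoea, with δ = 1 and 0.5. Power is from the noncentral t. The slight extra variance from mixing participants with and without diarrhoea is ignored.

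**Formula.** Effect seen by the planned contrast = δ × (diarrhoea share in symptomatic − share in asymptomatic).

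**Case A: all diarrhoea cases in the symptomatic group.** The same number of cases k is used for both contrasts. Taking 12.2% of the 70 symptomatic gives 0.122 × 70 = 8.5, so k = 9. Taking 12.2% of all 105 gives 0.122 × 105 = 12.8, so k = 13.

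| Cases k | δ | Planned effect δ × k/70 | Power, planned 70 vs 35 | Direct contrast | Power, direct |
|---|---|---|---|---|---|
| 9 | 1 | 9/70 = 0.129 | 9% | 9 vs 96 | 81% |
| 13 | 1 | 13/70 = 0.186 | 14% | 13 vs 92 | 92% |
| 13 | 0.5 | 0.5 × 0.186 = 0.093 | 7% | 13 vs 92 | 39% |

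**Case B: diarrhoea in both groups, δ = 1.**
- 20% vs 10%: effect 0.10 SD, power 8%.
- 30% vs 10%: effect 0.20 SD, power 16%.
- 50% vs 10%: effect 0.40 SD, power 48%.
- Equal shares: effect 0, so the contrast rejects at the 5% error rate and says nothing about the hypothesis.

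**Likely size of the diarrhoea subgroup**, applying the background rates to all 105:
- 0.064 × 105 = 6.7, about 7.
- 0.122 × 105 = 12.8, about 13.
- (0.064 + 0.122) × 105 = 19.5, about 20, if the two rates do not overlap.

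The 95% confidence interval for the direct difference has half-width 1.98 × √(1/k + 1/(105 − k)) SD. That is 0.78 SD for k = 7, 0.59 SD for k = 13 and 0.49 SD for k = 20.

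**The case against.** The strongest reply is that the study can test the hypothesis. All 105 participants are to be scanned and keep a bowel diary, endpoint 3 already splits by diarrhoea, and an analysis plan not available here could hold one more exploratory comparison. This stands in part. A reader might infer that the trial is unable to test hypothesis 3; that is true of the listed endpoints, not of the data. The point remains because the protocol itself fixes the contrast for these measures, identically in synopsis and body, and it is not the one the hypothesis describes.

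Three further readings are tempting and not supported:

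- **That the protocol's own figures show most symptomatic participants to be free of diarrhoea.** The rates of 6.4% and 12.2% are for diverticular patients generally, and the same section reports frequent lower abdominal pain in only 16.5% of patients with diverticulosis. It also links diverticulosis with diarrhoea-predominant and mixed IBS in the over-65s. The share among clinic patients selected for pain is unknown and could be higher. How severe the dilution is depends on it: at 50% vs 10% much less is lost.
- **That the hypothesis claims equivalence with D-IBS and so needs a D-IBS arm or an equivalence test.** The wording can fairly be read as a directional pattern already reported elsewhere. What stands is that the study recruits no D-IBS participants, so any likeness can only be described against external data.
- **That a null on endpoint 4 will be taken to refute hypothesis 3.** Nothing in the protocol says so; it is a risk of misreading, not a stated decision rule.

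The direct contrast should not be oversold either. Its 81-92% power rests on an assumed 1-SD shift.

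**Conclusion.** The mismatch holds on the text alone. Hypothesis 3 is about diarrhoea-predominant DD, the only bowel-water and lumen endpoint compares groups defined by pain, and the split by diarrhoea is planned only for adiponectin and leptin. Following the listed endpoints leaves the hypothesis untested.

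The numerical size is illustrative. It rests on an assumed effect confined to participants with diarrhoea and on assumed diarrhoea shares. In the range worked above, the planned contrast has low power for that effect unless diarrhoea is much commoner in the symptomatic group, and none beyond the error rate if the shares are equal. The direct contrast does better at the same shift, but is itself weak for a moderate one.

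This is a should-fix. A reader might want to grade it higher, but it concerns one of six secondary endpoints in a study that calls itself a pilot. The primary endpoint, the sample size and recruitment are unaffected.

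**What to change.** 1. Extend secondary endpoint 4 with a pre-specified comparison of small bowel water, colonic water and lumen diameter in DD participants with vs without diarrhoea.
2. Give one definition of diarrhoea, taken from the 14-day diary and shared with secondary endpoint 3. State how it handles incomplete diaries, since the Compliance section accepts 10 days or more.
3. Label the comparison exploratory and report estimates with confidence intervals, because the subgroup may be only about 7-20 of 105.
4. Restate hypothesis 3 as that directional contrast and keep all three predictions, including increased colonic water.
5. Make the likeness to D-IBS an explicitly descriptive comparison with external data.

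The existing symptomatic vs asymptomatic comparison can stay. The cost is a wording change and one added analysis on data already being collected, with no extra participants, scans or visits. The price is wide intervals.

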## PRIMARY OBJECTIVE

Difference in the volume of visceral fat compared to abdominal subcutaneous fat between symptomatic and asymptomatic DD groups

## SECONDARY OBJECTIVES

Differences between:

1. Adiponectin and leptin serum levels between symptomatic and asymptomatic DD groups
2. The incidence of diarrhoea between participants with a BMI <25Kgm-2 and those >25Kgm-2.
3. Adiponectin and leptin serum levels between DD groups with and without diarrhoea
4. Small and large bowel water and lumen diameter in symptomatic and asymptomatic DD groups
5. Calprotectin levels between symptomatic and asymptomatic DD groups.
6. Microbiological gut profile between symptomatic and asymptomatic DD groups.

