# STUDY BACKGROUND INFORMATION AND RATIONALE

## Diverticular disease

Colonic diverticulosis is the most common structural abnormality of the colon, yet our understanding of it is rudimentary. It affects 5% of people in their 5th decade and up to 66% of the elderly population in the United Kingdom[1]. It is responsible for substantial morbidity with 68,000 hospital admissions recorded per year in the UK and it contributes to about 2,000 deaths.

The definitions of diverticulosis and diverticular disease were established by the European Association for Endoscopic Surgery consensus development meeting in 1999[2]:

“Colonic diverticular disease is a condition seen mostly in the sigmoid region. It is characterized structurally by mucosal herniation through the colonic wall, generally accompanied by muscular thickening, elastosis of the taenia coli, and mucosal folding. This condition may be asymptomatic (*diverticulosis*) or associated with “symptoms,” termed *diverticular disease,* which may be complicated or uncomplicated. The term *diverticulitis* is used to indicate superadded inflammation involving the bowel wall. Other pathologic complications include perforation, fistula, obstruction, and bleeding.”

Studies using national databases of hospital admissions suggest its incidence and/or complications are increasing. A recent study from the United States reported a 26% increase in admission for acute diverticulitis between 1998 and 2005. The rise in admission rates were greatest in younger patients e.g. 45-64 years and 18-44 years[3].

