# STATISTICS

### Methods

Statistical analysis will carried out with the use of Prism 4 (GraphPad Software Inc, San Diego, CA). Comparisons between groups were performed by using 2-tailed unpaired *t* test or the Mann–Whitney's *U* test, for normal and non-normal data respectively by [name] and [name]

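### Secondary endpoint 3 compares adipokines by diarrhoea status without allowing for the 2:1 recruitment on pain, so it may partly repeat endpoint 1

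*Protocol*

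**What the plan says.** The protocol lists two separate adipokine comparisons under Secondary Objectives, repeated in the synopsis. Item 1 is "Adiponectin and leptin serum levels between symptomatic and asymptomatic DD groups". Item 3 is "Adiponectin and leptin serum levels between DD groups with and without diarrhoea".

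The Participant groups section plans three groups of 35. Two are symptomatic, split by a somatic symptom score, and the third is "35 participants with asymptomatic DD". The Inclusion criteria decide who is symptomatic: "Symptomatic disease is define as lower abdominal pain >1hr on 3 or more days per month for longer than 3 months". The sample is therefore 70 to 35 on pain.

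Under Statistics, Methods, the one analysis sentence reads "Comparisons between groups were performed by using 2-tailed unpaired" t test, with the Mann–Whitney test for non-normal data. Nothing there stratifies item 3 by recruitment group or limits it to some of the groups.

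Under Hypotheses, the second expects lower adipokine levels in symptomatic patients than in non-symptomatic controls. The first expects both painful symptoms and loose stool to rise with the visceral share of fat.

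**The concern.** Item 3 re-sorts the same people by diarrhoea, but the mix of people was set by pain. An unadjusted comparison by diarrhoea is confounded by pain when two things hold: adipokines differ by pain status, and diarrhoea is more frequent in the pain groups. The protocol predicts the first outright in hypothesis 2. Hypothesis 1 makes the second plausible, because it ties pain and loose stool to the same fat depot.

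If both hold, a positive item 3 would in part be the item 1 result seen again, and the report could claim an adipokine–diarrhoea link that does not exist within either recruitment group. Matching the groups on age and sex does not remove this.

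**Working it through.** **Plan's own figure.** The protocol gives no calculation for item 3. Its only sample-size figure (35 per group, 30% difference in visceral fat, 90% power, p<0.05) concerns the primary endpoint and states no SD, so it cannot be reproduced. Back-solving gives a standardised difference of (1.960 + 1.282) × √(2/35) = 0.775. This serves only as a reference for what the study regards as detectable.

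**Inputs from the protocol.** 70 symptomatic and 35 asymptomatic participants; unadjusted two-sample test; chronic diarrhoea in 12.2% of diverticular patients (Altered bowel habit and diverticular disease).

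**Assumptions.** Diarrhoea has no effect on adipokines. The pain-related adipokine difference is d = 0.5 or 0.8 SD. The diarrhoea rate is q among the symptomatic (12.2%, 30% or 50%) and r among the asymptomatic (0, q/2 or q).

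**Step 1: share carried over.** The expected false difference is d times

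P(symptomatic | diarrhoea) − P(symptomatic | no diarrhoea) = 70q/(70q + 35r) − 70(1−q)/[70(1−q) + 35(1−r)].

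Example, q = 30%, r = 0: 21/21 − 49/84 = 0.417. Example, q = 30%, r = 15%: 21/26.25 − 49/78.75 = 0.800 − 0.622 = 0.178.

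| q | r = 0 | r = q/2 | r = q |
|---|---|---|---|
| 12.2% | 0.363 | 0.148 | 0 |
| 30% | 0.417 | 0.178 | 0 |
| 50% | 0.500 | 0.229 | 0 |

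**Step 2: false-positive rate.** By normal approximation with q = 30%, r = 0, d = 0.5, the bias is 0.5 × 0.417 = 0.208. The standard error is √[1/21 + (1 + 0.417 × 0.583 × 0.25)/84] = 0.245, so the ratio is 0.85. The two-sided error is Φ(0.85 − 1.96) + Φ(−0.85 − 1.96), about 13.6%. Simulating the pooled t test (40,000 runs per case, normal data, counts fixed at their rounded expected values) gives slightly lower figures:

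| q | r = 0, d = 0.5 | r = 0, d = 0.8 | r = q/2, d = 0.5 | r = q/2, d = 0.8 |
|---|---|---|---|---|
| 12.2% | 7% | 11% | 5% | 5% |
| 30% | 12% | 23% | 6% | 8% |
| 50% | 21% | 44% | 8% | 12% |

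With r = q the rate is no more than about 5%. A symptomatic-only comparison stays at 5% throughout.

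**Step 3: price of restricting to the 70.** If r = 0, the standard error rises by the ratio √[1/(70q) + 1/(70 − 70q)] / √[1/(70q) + 1/(105 − 70q)], which is 1.02, 1.07 and 1.15 at q = 12.2%, 30% and 50%. If r = q, the ratio is √(105/70) = 1.22.

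**The case against.** A reader might infer something stronger: that diarrhoea cannot occur in the asymptomatic group, so that all 35 sit in the no-diarrhoea arm by design. The background gives some support, since the consensus definition it cites says "This condition may be asymptomatic" and contrasts that with having symptoms. But this is background, not an eligibility rule. The working definition of symptomatic disease is pain alone, no exclusion criterion mentions diarrhoea, and item 3 does not assign the asymptomatic group to either arm. Item 2 looks at "The incidence of diarrhoea between participants with a BMI <25Kgm-2 and those >25Kgm-2" without limiting it to symptomatic participants, and the bowel diary is asked of participants generally. The background also reports altered bowel habit in 28.5% and frequent pain in 16.5% of patients with diverticulosis. If these share a base, at least 28.5 − 16.5 = 12.0 points have altered habit without frequent pain (constipation included, so this is not a diarrhoea rate). Nor would the whole of a pain-related difference carry over: even with no diarrhoea among the 35, the share is 36% to 50%.

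What remains of the opposing case is that this is ordinary confounding of unknown size in an exploratory endpoint of a pilot study. Item 3 asks for a difference, not a pain-independent effect, and conditioning on pain answers a narrower question. A symptomatic-only analysis is already compatible with its wording, and covariates are often left to an analysis plan. All of that is fair, and it limits the weight of the point. It does not remove it: the protocol names an unadjusted test and no stratification, and an analysis plan that followed that text would inherit the problem.

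**Conclusion.** The point stands in conditional form. Item 3 is confounded by recruitment group to the extent that diarrhoea is commoner in the symptomatic groups and adipokines differ by pain status. The protocol predicts the latter and makes the former plausible, but establishes neither.

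The consequence ranges from nothing (equal diarrhoea rates), through modest (half the rate in the asymptomatic group), to material (no diarrhoea there and a frequent symptom among the rest). At the protocol's own 12.2% diarrhoea figure it is small: a false-positive rate of about 7% to 11% at worst. The larger figures rest on assumed diarrhoea rates of 30% to 50%. The pain-related differences of 0.5 to 0.8 SD are assumed throughout. The documents do not support saying that the design itself forces the error.

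**What to change.** State in item 3, in both the synopsis and Secondary Objectives, that the diarrhoea comparison of adiponectin and leptin will include symptomatic/asymptomatic recruitment group as a factor in all 105 participants, or will be restricted to the symptomatic participants. Amend the Statistics section to match. Both options work whether or not people with painless diarrhoea are admitted to the asymptomatic group.

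The cost is wording only, with no new data. Restriction raises the standard error by about 2% to 15% if no asymptomatic participant has diarrhoea, and by up to about 22% if the rates are equal. The factor model is therefore the better default, because it keeps whatever information the 35 carry. Either way, the result must be read as a diarrhoea difference within symptom group.
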